## Abstract

**Background:**

Hepatic resection is currently still the best choice of therapeutic strategies for liver cancer, but the long-term survival rate after surgery is unsatisfactory. Most patients develop intra- and/or extrahepatic recurrence. The reasons for this high recurrence rate are not entirely clear. Recent studies have indicated that ischemia-reperfusion injury to the liver may be a significant factor promoting tumor recurrence and metastasis in animal models. If this is also true in humans, the effects of the Pringle maneuver, which has been widely used in hepatectomy for the past century, should be examined. To date, there are no reported data or randomized controlled studies examining the relationship between use of the Pringle maneuver and local tumor recurrence. We hypothesize that the long-term prognosis of patients with liver cancer could be worsened by use of the Pringle maneuver due to an increase in the rate of tumor recurrence in the liver remnant. We designed a multicenter, prospective, randomized surgical trial to test this hypothesis.

**Methods:**

At least 498 eligible patients from five participating centers will be enrolled and randomized into either the Pringle group or the non-Pringle group in a ratio of 1:1 using a permuted-blocks randomization protocol. After the completion of surgical intervention, patients will be included in a 3-year follow-up program.

**Discussion:**

This multicenter surgical trial will examine whether the Pringle maneuver has a negative effect on the long-term outcome of hepatocellular carcinoma patients. The trial will also provide information about prognostic differences, safety, advantages and disadvantages between Pringle and non-Pringle surgical procedures. Ultimately, the results will increase the available information about the effects of ischemia-reperfusion injury on tumor recurrence, which will be of immense benefit to general surgery.

**Trial registration:**

http://www.clinicaltrials.gov NCT00725335

## Background

Hepatocellular carcinoma (HCC) is one of the most common cancers worldwide, and has been ranked the second leading cancer killer in China since the 1990s [1]. Chronic hepatitis B virus (HBV) infection is the most common etiology in China [2].

Curative resection remains the best choice of HCC therapeutic strategies to date, but local tumor recurrence and remote metastasis unfortunately occur in many patients who have undergone surgery. Although there have been great advances in the diagnosis and treatment of HCC, the long-term prognosis is still unsatisfactory due to a high incidence of tumor recurrence, ranging from 50% to 60% [3-6]. The reason for this high recurrence rate is not entirely clear. Locoregional tumor recurrence with concomitant hepatic decompensation is the main cause of death. It is suggested that further strategies may be needed for the prevention and treatment of early and late recurrence [7].

The Pringle maneuver is a classical surgical technique widely used during hepatectomy since its advent in 1908[8]. During hepatic resection, severe bleeding represents a major life-threatening risk [9,10]. The Pringle maneuver (continuous or intermittent clamping of the hepatic artery and portal vein) is routinely used to reduce intraoperative bleeding [11,12]. It seems inevitable that maneuver causes ischemia-reperfusion (I/R) injury, resulting in complex metabolic [13,14], immunological [15], and microvascular [16-18] changes, which together might contribute to hepatocellular damage and dysfunction[13,19]. Over the past century, the effects of the Pringle maneuver have been widely discussed [8,20-32]. From the reported data, we know that the technique can significantly reduce blood loss during hepatectomy, meanwhile damaging the liver remnant through the I/R injury. Interestingly, the effects of the Pringle maneuver on the prognosis of oncology patients and on the behavior of tumor cells have not been specifically discussed. It remains unknown whether tumor recurrence and metastasis can be influenced by this surgical stress.

However, this possibility has been raised by the results of recent animal studies [33,34]. It has been shown that surgical stress, such as I/R injury, might cause delayed damage to the residual liver (“soil”), and may also affect the behavior of the tumor cells (“seeds”) by activating cell invasion and migration signal pathways, thus accelerating tumor recurrence. I/R injury tends to disrupt normal liver tissues and create an environment that may promote tumor recurrence. Hepatic resection will also induce tumor cells to become more aggressive by promoting the production of cytokines by nonparenchymal liver cells [35]. From the results of these studies, it can easily be concluded that I/R injury to the liver remnant may be a significant factor promoting tumor recurrence and metastasis in experimental animal models. Animal models may introduce potentially important concepts related to the mechanisms involved in tumor recurrence associated with surgical stress, specifically hepatic I/R injury. Furthermore, the promotion of liver metastasis by hepatic I/R injury during liver resection has been reported in colon cancer patients [36,37], and minimization of I/R injury can attenuate metastasis of colorectal cancer to the liver [38-40]. Liver transplant recipients with HCC who receive living-donor grafts experience a higher recurrence rate [41,42] due to the more severe acute-phase injury to the liver graft.

For primary liver cancer patient undergoing hepatectomy, the effects of I/R injury on tumor recurrence need to be determined. Because use of the Pringle maneuver during hepatic resection will lead to I/R injury to the liver remnant, we can rationally deduce that it may harm liver function, make the tumor cells more aggressive, and increase the likelihood of recurrence. If this is found to be true in humans, routine use of the Pringle maneuver should be re-evaluated. It is unfortunate that there are currently no reported data or randomized controlled studies examining this issue.

### Our hypothesis

We hypothesize that the high incidence of tumor recurrence and the poor long-term prognosis of patients with HCC might be partly due to the I/R injury resulting from use of the Pringle maneuver during hepatectomy. If possible, this procedure should be avoided or revised when performing a hepatectomy on cancer patients [43]. In a clinical setting, many factors such as blood loss, blood transfusion, liver function, and HBV load affect the prognosis of cancer patients. These factors may each have different, and sometimes even opposing, effects on laboratory test results. However, evaluation of the effects of the Pringle maneuver remains an important and urgent issue in liver surgery, which may lead to a significant change to our current knowledge. We therefore designed a multicenter, prospective, randomized trial to test our hypothesis.

## Methods

### Aims of the study

This trial aims to assess the long-term effects of the Pringle maneuver on the rate of tumor recurrence after curative resection of HCC. The effects on disease-free survival, overall survival, operative morbidity and mortality, duration of operation, blood loss, transfusion requirements, hospital stay, intensive care unit stay, and blood test results with prognostic relevance, will be examined. The trial will test whether hepatic resection without the Pringle maneuver reduces recurrence rate and improves disease-free survival rate.

### Trial population

Our study group includes researchers in five leading hospitals in China (Southwest Hospital, Chinese PLA General Hospital, Zhongshan Hospital, Nanjing Drum Tower Hospital, and the First Affiliated Hospital of SunYet-Sen University) located in the southwestern, northern, eastern, middle, and southern parts of China, respectively. All eligible patients from these five participating hospitals with a clinical diagnosis of HCC with infection will be enrolled. The study will include patients’ aged 18 years or older undergoing potentially curative (R0) resection, if preoperative imaging indicates that R0 resection can be undertaken both with and without the Pringle maneuver. Patients with extrahepatic disease, severe liver cirrhosis, or tumor-positive lymph nodes in the abdomen or hepatoduodenal ligament will be excluded. We anticipate that 50 eligible cases per month will be enrolled in the trial. A detailed list of all eligibility criteria follows.

### Eligibility criteria

 1. Aged from 18 to 65 years, no gender restriction.

 2. Clinical diagnosis of resectable HCC.

 3. Liver function tests showing Child-Pugh grade A and clearance of indocyanine green at 15 minutes (ICG-R15) less than 15%.

 4. Tumor nodes in the liver which can be radically excised.

 5. No preoperative anti-cancer therapy.

 6. Written informed consent from the patient or legal guardian prior to enrollment in the study.

### Exclusion criteria

 1. Pregnancy.

 2. Extrahepatic tumor or lymph node metastasis.

 3. 3.Tumor invasion or thrombosis in the portal vein, hepatic vein, or inferior vena cava.

 4. Surgical marginal positive.

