### Study design

This study is funded by the National Major Science and Technology Project of China on the prevention and treatment of infectious diseases, for human immunodeficiency virus and HBV [2008ZX10002-026]. This clinical trial is a registered [NCT00725335], prospective, intraoperatively randomized multicenter trial of patients undergoing curative resection for HCC. The patients will be stratified by center and allocated to groups by a permuted-blocks randomization protocol. The primary objective of this study is to compare the disease free-survival rates at 1, 2, and 3 years postoperatively between the two groups. We hypothesize that the long-term prognosis of patients who have undergone curative resection will be worse in the control group (Pringle maneuver) than in the experimental group (non-Pringle maneuver).

The detailed study design is shown in Figure1.

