### Incision lines and decision-making

Specific teams of surgeons have been designated in each center participating in this trial, and have completed the operative and postoperative management training for following the protocol. The abdominal incision can be decided according to the surgeon’s preference. A complete exploration of the abdomen and an intraoperative ultrasound evaluation of the whole liver will be performed to decide whether curative resection is feasible. If necessary, frozen section biopsies will be taken to evaluate suspicious lesions or lymph nodes. If both intervention procedures seem possible to the surgeon, randomization will be performed at this time point.

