### Experimental group (group a, non-Pringle group)

The liver will be mobilized from the retroperitoneum and the peripheral ligament. Anatomical liver resection is preferable. If anatomical resection is not possible, a surgical margin of more than 2 cm should be achieved, except if the location of tumor nodes makes this impossible (e.g., close to the inferior vena cava or portal vein).The resection method and surgical margin will be recorded for analysis. The liver parenchyma can be resected according to the surgeon’s preference and local standards (CUSA, Tissue-link.). The Pringle maneuver will not be used, and hepatic inflow and outflow will be maintained. For safety, the surgeon may use the Pringle maneuver if major bleeding occurs.

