### Control group (group B, Pringle maneuver group)

After mobilization, the Pringle maneuver will be performed. The same approach will be used for hepatic parenchymal transection as in the experimental group. If necessary, the outflow of the hepatic vein can be controlled, and this factor will be analyzed. For safety, the surgeon may change the surgical technique at any time during the operation.

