### Sample size calculation and data analysis plan

The sample size of this trial was calculated using data from our previous experience and from the published literature. There are currently no data from randomized controlled trials showing the recurrence rate of HCC after hepatectomy without the Pringle maneuver. Most studies used the Pringle maneuver. This trial plans to have equal numbers of control and experimental subjects, and a 36-month follow-up period. The median survival time after the treatment that the control group will receive has been reported to be 26 months [24,44-50]. We anticipate a10-month difference in the median recurrence-free survival time between the experimental and control groups. If median survival times in the control and experimental groups are 26 months and 36 months, respectively, we will need to include 249 experimental subjects and 249 control subjects to be able to reject the null hypothesis that the experimental and control survival curves are equal with a probability (power) of 0.800. The Type I error probability associated with this test of the null hypothesis is 0.05.

Data for primary and secondary outcome measures will be analyzed using the SPSS statistical software package (SPSS UK Ltd., Woking, U.K.). Analysis will include standard descriptive statistics, Student’s t tests, correlation and regression, and two-way (group x time) repeated measures ANOVA to examine differences between the groups over time. Survival analysis will be performed. Statistical significance will be set at p < 0.05and all tests will be two-tailed. Subgroup stratified analysis will be performed according to tumor size, tumor encapsulation, Edmondson’s grade, HBV load, ischemic time, blood loss, and transfusion. The intention-to-treat analysis will be used for the patients whose portal triad clamping was changed due to safety reasons.

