### Randomization, stratification, and blinding

This is a randomized multicenter study. After giving informed consent and being enrolled in the study, patients will be randomized into different groups in the operating room after surgical exploration. The permuted-blocks randomization protocol will comprise five separate randomization lists, one for each participating hospital, and will be centrally managed by the Clinical Trial Center of the lead hospital, the Third Military Medical University. When an eligible case is enrolled, the Clinical Trial Center will be called and a randomization number will be assigned according to the designated list. Because there are two groups in this trial, the block sizes will be 4, 6, and 8 and will be randomly assigned. Patients will be stratified by site and randomized in a ratio of 1:1 into the two groups. Patients and outcome assessors will be blinded to achieve a minimum bias.

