### Follow-up

Patients who have completed the interventions will be included in the standard follow-up program. Follow-up visits will be at 1, 3, 6, 9, and 12 months and then every 6 months until 3 years after their operation. Each visit will include physical examination, tumor marker tests, liver function tests, chest x-ray, and ultrasound examination. In addition, enhanced CT scans of thorax and abdomen will be performed at 3, 6, 12, 18, 24, 32, and36 months postoperatively. Additional investigations including 18 F-fluorodexyglucose positron emission tomography scan, magnetic resonance imaging, or digital subtraction angiography will be scheduled as required to investigate possible tumor recurrence. At each visit, a follow-up evaluation form will be completed. If tumor recurs, the patient will be hospitalized and treated according to the clinical situation.

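### A positive surgical margin is an exclusion criterion, yet patients are randomised before the liver is cut, so the criterion can only remove patients after allocation

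*Protocol article*

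**What the plan says.** The fourth item under Exclusion criteria reads "Surgical marginal positive", with no qualification about when or how it is judged.

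Three sections fix the time of randomisation:
- Study design describes an "intraoperatively randomized multicenter trial of patients undergoing curative resection for HCC".
- Incision lines and decision-making, after describing exploration and intraoperative ultrasound, says: "If both intervention procedures seem possible to the surgeon, randomization will be performed at this time point".
- Randomization, stratification, and blinding says that "patients will be randomized into different groups in the operating room after surgical exploration".

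The operation then proceeds by arm. In the control group, "After mobilization, the Pringle maneuver will be performed", and transection follows. The Experimental group section treats the margin as a result of the operation: "The resection method and surgical margin will be recorded for analysis".

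On the analysis set, the data analysis plan says: "The intention-to-treat analysis will be used for the patients whose portal triad clamping was changed due to safety reasons". Clinical evaluation repeats this for changed clamping and adds one exclusion after surgery, for tumours that prove not to be primary HCC, read by two professionals blinded to treatment. Follow-up opens with: "Patients who have completed the interventions will be included in the standard follow-up program".

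**The concern.** An exclusion criterion should rest on what is known before allocation, or at least on something that allocation cannot change. Margin status is neither. It is produced by the resection, and the two arms carry out the resection under conditions that the trial deliberately makes different.

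The article itself supplies the links. The Background says that clamping substantially reduces blood loss. Trial population requires R0 resection to look feasible on imaging both with and without the maneuver, which treats technique as relevant to R0. The Discussion lists surgical margins among the factors that may affect outcome and says such factors are dealt with through the eligibility criteria and subgroup analysis.

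If margin-positive patients are dropped, the groups compared are no longer the groups randomised. Should one technique leave more positive margins, part of its effect on recurrence is deleted. Should the patients dropped differ in prognosis between arms, a difference can appear where none exists.

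**Working it through.** **1. Order of events.** Consent, exploration and ultrasound, judgement that both techniques are possible, randomisation, clamping or no clamping, transection, margin. The criterion depends on the last step and allocation is the fourth, so it cannot be applied before allocation. Resectability as judged beforehand is already covered by Trial population, by the fourth eligibility criterion and by Incision lines and decision-making. What the margin criterion adds is the achieved result.

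**2. The plan's own sample size.** Inputs: medians 26 and 36 months, two-sided alpha 0.05, power 0.80 (data analysis plan); 9 months of recruitment and 36 of follow-up (Duration of the trial). I assume exponential times and uniform accrual.
- HR = 26/36 = 0.722; ln HR = −0.3254.
- Schoenfeld events = 4 × (1.960 + 0.842)² / 0.3254² = 297.
- Mean event probability 0.600, so N = 297/0.600 = 495.
- The variant (z_a + z_b)² × (1/p1 + 1/p2) / (ln HR)², with p1 = 0.660 and p2 = 0.541, gives 249.4 per arm.

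The stated 249 per arm reproduces.

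**3. Power if patients are removed.** The full 498 patients give 498 × 0.600 ≈ 299 events and power 80.3%. The removal rates below are assumed.

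| Removed | Patients left | Power |
|---|---|---|
| 2% | 488 | 79.5% |
| 5% | 473 | 78.3% |
| 10% | 448 | 76.1% |

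**4. Illustration A: technique affects only the margin.** Assumptions: margin-negative median 26 months in both arms, hazard 2.5 times higher after a positive margin, no direct effect of clamping, censoring at 36 months.
- 36-month recurrence-free proportion: margin-negative 2^(−36/26) = 0.383; margin-positive 2^(−2.5 × 36/26) = 0.091. The gap is 0.292.
- The difference hidden by the exclusion is the difference in margin-positive rates × 0.292.
- The all-randomised HR (non-Pringle to Pringle) solves the large-sample Cox score equation for the two mixtures.

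| Margin-positive, Pringle vs non-Pringle (assumed) | All-randomised HR | HR after exclusion | Hidden 36-month difference |
|---|---|---|---|
| 3% vs 8% | 1.045 | 1.00 | 0.05 × 0.292 = 1.5 points |
| 5% vs 15% | 1.09 | 1.00 | 0.10 × 0.292 = 2.9 points |

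With 3% vs 8%, the ratio of hazards at time zero is 1.12/1.045 = 1.072. The Cox estimate is lower because high-risk patients are used up early. Swapping the rates between arms inverts the hazard ratios.

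**5. Illustration B: no effect on recurrence, but selective removal.** Assumptions: 15% of patients have a poor prognosis (median 13 months, others 30), and removals come only from them. With a fraction r removed, the 36-month proportion is [(0.15 − r) × 0.147 + 0.85 × 0.435]/(1 − r).
- r = 2%: 0.397. r = 5%: 0.405. r = 10%: 0.419.
- 2% vs 5% creates a false difference of 0.8 points, and 2% vs 10% one of 2.2 points, in favour of the arm with more removals.
- Equal rates with the same type of patient removed give no bias.

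**The case against.** **The effect is small and its direction open.** With about 299 events, the standard error of log HR is about 2/√299 = 0.116. The shifts in illustration A (ln 1.045 = 0.044 and ln 1.09 = 0.087) are about 0.4 and 0.75 of that, against a planned HR of 0.722. The rules on R0 feasibility, anatomical resection and margin width should make positive margins uncommon. No section says that clamping changes margin status, and surgeons may clamp in the non-Pringle arm if major bleeding occurs, which narrows the contrast where the mechanism would act. All of this stands. A reader might infer that the exclusion favours the trial's hypothesis; that follows only if non-Pringle surgery gives more positive margins, which the article does not establish.

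**Intention-to-treat may be general.** A reader might take the analysis sentence to confine intention-to-treat to crossovers. It does not say so, and the wording in Clinical evaluation presupposes a wider intention-to-treat analysis. The supportable statement is narrower: the principle is spelled out only for changed clamping, and nothing sets it above the margin exclusion.

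**Follow-up is not shown to be lost.** A reader might also infer that margin-positive patients leave follow-up, because that section speaks of completed interventions. The Abstract puts patients into a 3-year programme once surgery is over, and the Figure 1 caption has each patient followed for 3 years. The phrase most plausibly means after surgery.

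**The criterion may mean expected margins.** The text does not say so, and expected resectability is covered elsewhere. If that was the intent, the wording still needs changing.

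**Conclusion.** The timing conflict is certain from the article's own text: as written, the plan removes patients on a prognostic result that arises after randomisation and that the assigned technique may affect. No statement keeps those patients in the analysis. The exclusion for non-HCC is different in kind, since tumour type is fixed before allocation and is read blind.

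Size and direction are unknown because no margin rates are given. Under the assumed rates the hidden effect is modest, an HR of about 1.045 to 1.09 or 1.5 to 2.9 points at 36 months, and lost power is a minor matter. The point should be settled before analysis because of what it does to the randomised comparison, whatever the illustrative figures. The documents do not support a claim that the result is tilted towards the hypothesis or that patients are lost to follow-up.

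**What to change.** - **Exclusion criteria:** replace the margin item with what is judged before randomisation, namely that curative resection is considered feasible at exploration.
- **Data analysis plan and Clinical evaluation:** state that every randomised patient is analysed in the assigned arm in the primary analysis, the only exception being non-HCC on blinded pathology.
- **Margin status:** report it by arm as an outcome, and give the margin-negative analysis as a sensitivity analysis. The margin is already to be recorded; that sentence stands under the experimental group, so say that it applies to both arms.
- **Follow-up (clarification only):** align the opening sentence with the Abstract and the Figure 1 caption, so that all randomised patients are followed for 36 months.

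The cost is a wording change and a few more patients kept on the existing visit schedule. The sample size of 498 stays as it is, and no surgical rule changes.
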